## 8.4. Frailty Phenotype assessments and geriatric scale

Frailty Phenotype assessments:

- Frailty phenotype assessment is also part of this study and will be evaluated from all participants as specified in the SoA.
- Frailty phenotype will be assessed for protocol-specific endpoints to evaluate its association with the study intervention.
- Frailty phenotype assessment will include (See SoA and Appendix 5 for further information):
  - Fried frailty phenotype criteria (40):
    - Unintentional weight loss (5% or 4.5 Kg or more during the last year).
    - Exhaustion Using the responses (YES/NO) to two statements of the depression scale CES-D.
    - Physical activity assessed by the short version of the Minnesota Leisure Time Activity questionnaire
    - Gait speed on a 4.6 m (15 feet distance) adjusted for gender and height.
    - Dominant hand grip strength in Kg adjusted for gender and BMI.

Patients will be classified as frail if they meet at least three of these criteria using the reference values of the Spanish population. Non-fragile patients will include pre-frail patients (those who meet 1 or 2 criteria) and fit patients (those without any of the criteria).

- Short Physical Performance Battery: The SPPB is based on three timed tasks: standing balance, walking speed, and chair stand tests. The timed results of each subtest are rescaled according to predefined cut-points for obtaining a score ranging from 0 (worst performance) to 12 (best performance).
- Hand-grip strength in the dominant hand, according to the protocol published by Mohd Hairi F et al. (41), and using the Jamar hydraulic hand dynamometer (Sammons Preston, Bolingbrook, IL, USA).

Geriatric scale:

- Mini-Nutritional Assessment. This includes a short questionnaire to screen for undernutrition in geriatric practice (44). Each answer provides a score and the sum of all

of them gives the screening score, ranging from 14 to 0 points, where 12-14 points represents a healthy nutritional state and 0-7 points represents malnutrition.

- Modified Rockwood Clinical Frailty Scale. This scale allows to determine the state of health deficit associated to ageing and in this study we used a modified version with 8 different frailty levels, ranging from a Fit state to a Very Severe Frailty State (45).
- Short Geriatric Depression Scale (Yesavage test).

## **8.5. Adverse Events (AEs), Serious Adverse Events (SAEs), and Other Safety Reporting**

The definitions of adverse events (AEs) and serious adverse events (SAEs) can be found in Appendix 4.

AEs will be reported by the participant (or, when appropriate, by a caregiver, surrogate, or the participant's legally authorized representative).

The investigator and any qualified designees are responsible for detecting, documenting, and recording events that meet the definition of an AE or SAE and remain responsible for following up all AEs OR AEs that are serious, considered related to the study intervention or study procedures, or that caused the participant to discontinue the study intervention (see Section 7).

The method of recording, evaluating, and assessing causality of AEs and SAEs and the procedures for completing and transmitting SAE reports are provided in Appendix 4.

SAEs will be reported to the trial's pharmacovigilance manager: [name], Head of Pharmacovigilance, Unidad de Ensayos Clínicos Hospital La Paz. [contact]. [name])

### **8.5.1. Time Period and Frequency for Collecting AE and SAE Information**

All SAEs will be collected from the signing of the informed consent form until the last follow-up visit at the time points specified in the SoA (Section 1.3).

All AEs will be collected from the signing of the informed consent until the last follow-up visit at the time points specified in the SoA (Section 1.3).

Medical occurrences that begin before the start of study intervention but after obtaining informed consent will be recorded as Medical History/Current Medical Conditions, not as AEs.

All SAEs will be recorded and reported to the sponsor or designee immediately and under no circumstance should this exceed 24 hours, as indicated in Appendix 4. As indicated in Appendix 4, those disease/disorder being studied or expected progression, signs, or symptoms of the disease/disorder being studied, don't meet the AE Definition, and therefore will not be considered SAEs if severe criteria are met, also not expedited reporting is needed. The investigator will submit any updated SAE data to the sponsor within 24 hours of it being available.

Investigators are not obligated to actively seek information on AEs or SAEs after conclusion of the study participation. However, if the investigator learns of any SAE, including a death, at any time after a participant has been discharged from the study, and he/she considers the event to be reasonably related to the study intervention or study participation, the investigator must promptly notify the sponsor.

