## 1. Protocol Summary

### 1.1. Synopsis

**Protocol Title:**

A double blinded, phase II, placebo controlled, single center randomized clinical trial to evaluate metformin compared with placebo for reversal of accelerated biological aging in persons living with HIV 50 years or older and with suppressed virologic replication.

**Brief Title:** Metformin vs placebo for reversal of accelerated biological aging in persons living with HIV 50 years or older and with suppressed virologic replication

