## **2.2. Background**

Aging refers to the changes that occur during an organisms' life-span, though the rate at which these take place varies widely (23). Consequently, such definition comprises the progressive deterioration of bodily functions over time. Normal human aging has been associated with a loss of complexity in a wide range of physiological processes and anatomic structures (24), leading to impaired function and increased morbidity and mortality. Metabolic, cardiovascular, neoplastic and neurodegenerative disorders as well as geriatric symptoms like frailty and immobility are a consequence of this physiological deterioration (9). Although it is evident that many elderly people reach advanced ages in healthy conditions, the prevalence of age-dependent disease and the average age of patients who enter the clinic is increasing. Millions of people die every year from these medical conditions associated to advancing age and the medical cost trying to mitigate them is staggering (25). Yet the risk of suffering age-related conditions in later life can be modified for most people by intervening in biological systems, through caloric restriction diet, exercise, and therapeutic interventions (26).

Certain disorders and diseases have some of the same effects as aging. HIV infection is one of these examples. It remains uncertain if HIV infection causes accelerated aging (age associated diseases occurring earlier than in the HIV negative population) or accentuated aging (age associated diseases occurring at the same age than in the HIV negative population but with increased frequency). However, what it is beyond doubt is that untreated HIV infection causes an accelerated aging of the human immune system, an alteration also known as immunosenescence. Indeed, HIV infection is considered a model of accelerated immunosenescence (27).

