Antiretroviral therapy (ART) has transformed the natural course of HIV infection into a chronic and manageable disease in which life expectancy among people living with HIV (PLWH) approaches that of the general population (28) This prolonged survival in PLWH has been linked with both an increased burden and a premature risk of suffering age-related comorbidities such as cardiovascular disease, cancer, cognitive impairment, osteoporosis and frailty (29,30). Mortality rates in HIV-infected populations range from 1.7- to 7.0-times those of HIV-uninfected populations (31). Thus, persons with HIV on ART have far less life-threatening acute illnesses but must confront issues related to the aging process.

Scientific efforts are underway to understand and intervene in the underlying processes of aging. From the cellular perspective, there are several mechanisms that are considered to affect the primary aging process, which include damage to the genetic material, epigenetic changes, telomere attrition, cellular senescence, proteostasis loss, mitochondrial dysfunction, deregulated nutrient sensing, altered intercellular communication and stem cell exhaustion (9). These hallmarks and their interconnectivity have led to a search for biomarkers of aging, biological

parameters that capture age-related changes and the susceptibility to disease and loss of function. Therefore, clinical interventions targeting the aging process should result in changes in biomarkers that will eventually delay the incidence, accumulation, clinical evolution and functional consequences of age-related diseases. Several biomarkers of aging have been postulated, as telomere length, epigenetic changes, levels of certain serum proteins, immunological markers, systemic inflammation parameters or metabolic and oxidative stress markers (32). However, the multi-factorial nature of aging makes it difficult to find a single measurement useful to determine biological age, so a combination of different parameters seems be appropriate.

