| Events Meeting the AE Definition                                                                                                                                                                                                                                                                                                                                                                                                                                                                                                                                                           |
|--------------------------------------------------------------------------------------------------------------------------------------------------------------------------------------------------------------------------------------------------------------------------------------------------------------------------------------------------------------------------------------------------------------------------------------------------------------------------------------------------------------------------------------------------------------------------------------------|
| 
 
• Any abnormal laboratory test results (hematology, clinical chemistry, or urinalysis) or other safety assessments (e.g., ECG, radiological scans, vital signs measurements), including those that worsen from baseline, considered clinically significant in the medical and scientific judgment of the investigator (i.e., not related to progression of underlying disease).
 
• Exacerbation of a chronic or intermittent pre-existing condition including either an increase in frequency and/or intensity of the condition.
 
 |

- New conditions detected or diagnosed after study intervention administration even though it may have been present before the start of the study.
- Signs, symptoms, or the clinical sequelae of a suspected intervention- intervention interaction.
- Signs, symptoms, or the clinical sequelae of a suspected overdose of either study intervention or a concomitant medication. Overdose per se will not be reported as an AE/SAE unless it is an intentional overdose taken with possible suicidal/self-harming intent. Such overdoses should be reported regardless of sequelae.

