#### Events **NOT** Meeting the AE Definition

- Any clinically significant abnormal laboratory findings or other abnormal safety assessments which are associated with the underlying disease, unless judged by the investigator to be more severe than expected for the participant’s condition.
- The disease/disorder being studied or expected progression, signs, or symptoms of the disease/disorder being studied, unless more severe than expected for the participant’s condition.
- Medical or surgical procedure (e.g., endoscopy, appendectomy): the condition that leads to the procedure is the AE.
- Situations in which an untoward medical occurrence did not occur (social and/or convenience admission to a hospital).
- Anticipated day-to-day fluctuations of pre-existing disease(s) or condition(s) present or detected at the start of the study that do not worsen.

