| 
d. Results in persistent or significant disability/incapacity
 
 
• The term disability means a substantial disruption of a person's ability to conduct normal life functions.
 
• This definition is not intended to include experiences of relatively minor medical significance such as uncomplicated headache, nausea, vomiting, diarrhea, influenza, and accidental trauma (e.g., sprained ankle) which may interfere with or prevent everyday life functions but do not constitute a substantial disruption.
 
                                                                                                                                                                             |
| 
e. Is a congenital anomaly/birth defect
                                                                                                                                                                                                                                                                                                                                                                                                                                                                                                                                                                                                                                                                                                             |
| 
f. Other situations:
 
 
• Medical or scientific judgment should be exercised by the investigator in deciding whether SAE reporting is appropriate in other situations such as significant medical events that may jeopardize the participant or may require medical or surgical intervention to prevent one of the other outcomes listed in the above definition. These events should usually be considered serious. 
 
○ Examples of such events include invasive or malignant cancers, intensive treatment for allergic bronchospasm, blood dyscrasias, convulsions or development of intervention dependency or intervention abuse.
 
 
 
               |

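### Section 8.5.1 restates the Appendix 4 disease-progression exclusion without its severity limit and extends it to SAEs, in a trial of ageing that never defines the disorder; the AE rules contradict each other

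*Protocol*

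**What the plan says.** Section 8.5.1, citing Appendix 4, states that "those disease/disorder being studied or expected progression, signs, or symptoms of the disease/disorder being studied, don't meet the AE Definition", and that these events "will not be considered SAEs if severe criteria are met, also not expedited reporting is needed". I read the severity wording in that sentence as meaning the seriousness criteria, since Section 10.4.3 keeps severity and seriousness apart.

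The source rule is in Appendix 4, in the Section 10.4.1 list of events that are not AEs. It is conditional: "The disease/disorder being studied or expected progression, signs, or symptoms of the disease/disorder being studied, unless more severe than expected" for the participant's condition.

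Neither Section 8.5 nor Appendix 4 says what the disorder is or which events count as its expected progression. The title says that the trial is designed "to evaluate metformin compared with placebo for reversal of accelerated biological aging in persons living with HIV". On ageing in general, Section 2.2 says: "Metabolic, cardiovascular, neoplastic and neurodegenerative disorders as well as geriatric symptoms like frailty and immobility are a consequence of this physiological deterioration". For people with HIV it adds that longer survival has been linked with a greater and earlier risk of "age-related comorbidities such as cardiovascular disease, cancer, cognitive impairment, osteoporosis and frailty".

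Other parts of Appendix 4 point the opposite way. Section 10.4.1 counts as AEs "New conditions detected or diagnosed after study intervention administration" and requires the sequelae of lack of efficacy to be reported when they fit the AE or SAE definition. Section 10.4.2, on other medically important situations, says: "Examples of such events include invasive or malignant cancers".

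**The concern.** Excluding expected progression is workable when the disease is narrow and its course can be listed. Here the condition treated is ageing, and the protocol's own background attributes several major disease groups to it. With no definition of the disorder, an investigator who follows Section 8.5.1 literally could class a new infarction, cancer or dementia as expected progression. It would then be neither an AE nor an SAE and would not be reported on an expedited basis.

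Three outputs depend on that classification: the AE and SAE data used for pharmacovigilance, the comparison of AE incidence and severity by arm in Section 9.4.4, and the grade 3 AE trigger in Section 10.1.5.1. A rule that lets individual judgement decide whether an event exists in the data also makes the arm comparison harder to interpret.

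**Working it through.** No figure in the protocol is at issue, so the check is a comparison of texts.

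1. **Section 8.5.1 against its source.** The Section 10.4.1 exclusion applies at AE level and exempts events worse than expected. Section 8.5.1 has no such exemption and spells the exclusion out for SAEs and expedited reporting. An unexpectedly severe event is therefore an AE under Appendix 4 and not an AE under Section 8.5.1.

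2. **What the disorder is.** The AE sections are silent. The candidates are HIV infection and accelerated ageing. The title and the primary objective point to ageing; nothing restricts the term to HIV.

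3. **What could count as its progression.** No list is given. Section 2.2 comes nearest, naming metabolic, cardiovascular, neoplastic and neurodegenerative disorders and frailty as consequences of ageing.

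4. **How one event is treated.** Take a cancer diagnosed after dosing.
   - Section 8.5.1, read literally with ageing as the disorder: it can be classed as not an AE, not an SAE and not expedited.
   - Section 10.4.1, events meeting the definition: it is a new condition, so an AE.
   - Section 10.4.2: malignant cancer is a named example of a serious event.
   - Section 7.1.1: the same diagnosis requires permanent discontinuation of study drug, so the protocol treats it as important to safety.

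   The first line cannot be reconciled with the others.

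5. **Whether an endpoint would recover the event.** The Section 3 endpoints are the epigenetic clocks, immune profile, inflammatory and ageing biomarkers, telomere length, the frailty battery, creatinine and viral reservoir. Infarction, stroke, cancer and fracture are not endpoints. An event dropped from AE reporting is not counted elsewhere in the planned analyses.

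6. **Effect on the safety review.** Section 10.1.5.1 lists two kinds of event. Deaths count regardless of causality, so the exclusion should not affect them there. Grade 3 AEs count when reported in more than 2 participants, so the third participant meets the trigger and one reclassified event can decide it. The planned early aggregated review covers 30 participants for 28 days: 30 × 28 = 840 participant-days, and 840 / 365.25 = 2.3 person-years. Any effect on that single review is small; the continuous monitoring in the same section runs throughout the study.

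**The case against.** The best reply is that Section 8.5.1 only paraphrases. Section 8.5 places the definitions in Appendix 4, and the disputed sentence itself defers to that appendix, which keeps the severity limit. Section 5.2 excludes people with a history of stroke, heart failure, dementia, myocardial infarction or cancer, so any of these on study is a new condition and hence an AE under Section 10.4.1. Inpatient admission is a seriousness criterion in Section 10.4.2. Sections 7.1.1 and 7.1.2 treat several of these diagnoses as reasons to stop study drug, not as expected background. Someone who follows Appendix 4 throughout would capture most of the events of interest.

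That stands, and it limits the point. It does not remove it. Section 8.5.1 is the section on collecting and reporting events, its wording is absolute, and it contradicts the appendix that it cites. Restoring the limit alone would also leave open what is expected when the disorder is unnamed.

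Three stronger readings are tempting and are not supported:

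- A reader might infer that serious age-related events will be lost, or that they would be most of the serious events seen. The protocol gives no event rate, no total SAE rate and no share of events that would be misclassified.
- A reader might infer that Section 2.2 calls these diseases consequences of accelerated ageing in HIV. The consequence wording concerns normal human ageing. For HIV the text reports a link with longer survival, and it says that whether HIV causes accelerated or accentuated ageing is uncertain. Nowhere does it call these diseases expected progression.
- A reader might infer that the exclusion disables the safety review. Only the grade 3 AE trigger and the AE input to continuous monitoring are exposed.

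**Conclusion.** The point holds as an internal contradiction in the safety-reporting rules. Section 8.5.1 drops a limit that its source contains, extends the exclusion to SAEs and expedited reporting, and applies it to a disorder that the AE sections do not define. In a trial of ageing, that wording permits a new age-related event to be left out of the AE and SAE data and of the outputs built on them, while Appendix 4 requires it to be included.

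The conclusion rests on a literal reading of Section 8.5.1 and on ageing being at least part of the disorder studied. If the disorder were HIV alone, less would be at risk, but the protocol does not say so. No numerical size can be attached. The change is worth making because the rule can misclassify serious events that no endpoint would count.

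**What to change.** Reconcile Section 8.5.1 with Sections 10.4.1 and 10.4.2:

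- Delete the sentence in Section 8.5.1 that excludes expected progression from AE, SAE and expedited reporting. At the least, restore the Appendix 4 severity limit there.
- State in Section 8.5.1 and in the matching Appendix 4 bullet that the exclusion covers only changes in the epigenetic clocks and research biomarkers. List those biomarkers by name, because some endpoints, such as creatinine and HbA1c, are also in the safety laboratory table in Appendix 2.
- State that new or worsening clinical events, including age-related disease, are AEs, and are SAEs with the normal reporting timelines when a seriousness criterion is met.

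The cost is a few sentences in an amendment and a few more SAE forms. No assessment, visit or analysis method changes.

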#### **8.5.2. Method of Detecting AEs and SAEs**

Care will be taken not to introduce bias when detecting AEs and/or SAEs. Open-ended and non-leading verbal questioning of the participant is the preferred method to inquire about AE occurrences.

#### **8.5.3. Follow-up of AEs and SAEs**

After the initial AE/SAE report, the investigator is required to proactively follow each participant at subsequent visits/contacts. All SAEs will be followed until resolution, stabilization, the event is otherwise explained, or the participant is lost to follow-up. Further information on follow-up procedures is provided in Appendix 4.

